## Abstract

**Background:**

Cardiovascular disease (CVD) is a group of disorders of the heart and blood vessels, such as coronary heart disease (CHD), cerebrovascular disease, and peripheral artery disease. CVD is the leading threat to global health, whether measured by mortality, morbidity, or economic cost. Long-term administration of aspirin, statins, beta-blockers, and angiotensin-converting enzyme inhibitors or angiotensin-receptor blockers improves survival in patients with stablished coronary heart disease. Nevertheless, adherence to prescribed medication is poor for long-term drug treatment.

**Objective:**

We aim to assess the relationship between adherences to the four pharmacological groups recommended for secondary prevention and the clinical outcomes of cardiovascular morbidity and mortality in patients with established CHD according to the level of adherence to these drugs in a population of incident cases of acute coronary syndrome (ACS).

**Methods:**

Population-based cohort study of patients with a first episode of ACS during 2006-2015 in the Information System for Research in Primary Care (SIDIAP) database. We will estimate adherence to these drugs. The primary endpoint is a composite of all-cause mortality, ACS, and ischaemic stroke. Bivariate analyses will be performed estimating odds ratios for categorical variables and mean differences for continuous variables. Hazard ratios for adherences will be calculated for outcome events using Cox proportional hazard regression models, and proportionality of hazards assumption will be tested.

**Results:**

We expect to estimate adherence to all four study treatments, the incidence of MACE, and to analyze if this incidence is associated with the level of drug adherence.

**Conclusions:**

We expect to find that adherent patients have a lower risk of the primary endpoints compared with nonadherent patients.

**Trial Registration:**

This study protocol was classified as EPA-OD by the AEMPS (IJG-EST-2017-01-2017-01, 07/04/2017) and registered in the EU PAS register (EUPAS19017, 09/05/2017).

## Introduction

Cardiovascular disease (CVD) is a group of disorders of the heart and blood vessels, such as coronary heart disease (CHD), cerebrovascular disease, and peripheral artery disease. CVD is the leading threat to global health, whether measured by mortality, morbidity, or economic cost [1]. In 2012, it was the leading cause of mortality worldwide, accounting for 31% of an estimated 56 million deaths from all causes. Also, CVD was responsible for the largest proportion of deaths for noncommunicable diseases under the age of 70 years, 37% of 16 million deaths [2].

Despite these numbers, the incidence of CVD death has decreased dramatically over the last four decades due to both population-level lifestyle changes in diet, smoking, and physical activity, and the development of effective interventions to treat individuals. The latter includes invasive procedures and effective drugs to tackle modifiable CVD risk factors [3].

A number of randomized clinical trials, meta-analyses and cohort studies have demonstrated that long-term administration of aspirin, statins, beta-blockers, and angiotensin-converting enzyme inhibitors (ACEI) or angiotensin-receptor blockers (ARB) improve survival in high-risk patients, particularly those with established CVD. Nevertheless, adherence to prescribed medication is poor for long-term drug treatment in CVD [1,4-6]. Different factors have been described to be related with long-term nonadherence [1,5-7].

In a recent cohort study conducted by Bansilal et al [4], 4015 patients who had suffered an acute myocardial infarction (AMI) were categorized according to their drug adherence to statin and ACEI into three categories: fully adherent (≥80% proportion of days covered [PDC]), partially adherent (40-79% PDC) or nonadherent (<40% PDC). Fully adherents had lower rates of major cardiovascular events (MACE) than partially adherents, 18.9% vs 24.7% (adjusted hazard ratio [HR] 0.81, 95% CI 0.69-0.94) and nonadherents, 18.9% vs 26.3% (HR 0.72, 95% CI 0.62-0.85).

In the cohort study conducted by Lafeber et al [8], 2706 CHD patients were included. Of them, 67% were treated with a combination of aspirin, statin, and at least one blood pressure (BP)-lowering agent for secondary prevention. After a median follow-up period of five years, the combination therapy compared with no combination showed lower rates for all events: AMI, HR 0.68 (95% CI 0.49-0.96); ischaemic stroke, HR 0.37 (95% CI 0.16-0.84); vascular mortality, HR 0.53 (95% CI 0.33-0.85); composite endpoint of the previous events, HR 0.66 (95% CI 0.49-0.88); and all-cause mortality, HR 0.69 (95% CI 0.49-0.96).

A population-based cohort study performed in Spain assessed adherence to secondary prevention drugs in a cohort of 7462 patients who survived an acute coronary syndrome (ACS) [6]. Medication adherence was evaluated by determining the PDC for each therapeutic group (antiplatelet agents, beta-blockers, ACEI or ARB, and statins) in the nine months following hospital discharge. Full adherence was defined as PDC75, at least 75% of days of the follow-up period covered by treatments dispensed. PDC75 for antiplatelet agents was reached by 5216 (69.9%) patients, for beta-blockers by 3231 (43.3%) patients, for ACEI/ARB by 3388 (45.4%) patients, and for statins by 4388 (58.8%). Only 3552 (47.6%) patients reached PDC75 for three or more therapeutic groups, whereas 1343 (18%) of patients did not reach PDC75 with any treatment. Some factors found to be related with nonadherence were older age, female sex, or copayment of drugs dispensed.

In a meta-analysis of 20 studies [9] in 376,162 patients assessing adherence to drugs for the primary or secondary prevention of a CHD event using prescription refill frequency, the estimated overall adherence to cardiovascular medications was only 57% (95% CI 50–64) after a median of 24 months, although it was superior in secondary prevention 66% (95% CI 56–75) than in primary prevention users (50%, 95% CI 45–56).

A large epidemiological study enrolled 7519 participants with established CVD from urban and rural communities in countries at various stages of economic development [10]. Use of antiplatelet drugs, beta-blockers, ACEI or ARB, and statins was assessed. Overall, 4421 (58.5%) individuals were not taking any of the four proven effective drugs, whereas 233 (3.1%) were taking all four drug types. Individuals recruited in high-income countries had had a CHD event or stroke a median of 6.0 years (interquartile range [IQR] 3.0–10.0) before inclusion. Although medication use increased in line with increase of country economic status, adherence rates in high-income countries were sparse too: 62.0% for antiplatelet drugs, 40.0% for beta-blockers, 49.8% for ACEI or ARB and 66.5% for statins.

A meta-analysis of randomised clinical trials assessed adherence to therapy comparing different dosing regimens in patients with chronic CVD.[11] The study showed that dosing regimens with once-daily administration, compared with two or more daily administrations, were associated with a significant 56% risk reduction of nonadherence to drug therapy (relative risk 0.44, 95% CI 0.35–0.54).

Due to the improvement of morbidity and mortality found with the quadruple drug therapy with antiplatelet, beta-blocker, ACEI or ARB, and statin in patients with established CVD, it is necessary to assess the long-term adherence to these drugs in the Catalan population and its relationship with cardiovascular events and mortality. Our hypothesis is patients with established CHD who adhere to drug therapy with the four recommended pharmacological groups have a lower risk of MACE and all-cause mortality compared with patients who do not adhere to drug therapy.

The main objective of our study is to assess the relationship between adherences to the four pharmacological groups recommended for secondary prevention and the clinical outcomes of cardiovascular morbidity and mortality in patients with established CHD. The outcomes which are included as components of the composite endpoint are all-cause mortality, ACS, and ischaemic stroke. The secondary objectives are: 1) to assess the incidence of the composite endpoint in patients who are adherent to treatment with all four drugs compared with patients who are adherent to any combination of three, two or one drug, or no drug; 2) to assess the relationship between baseline sociodemographic and clinical characteristics and adherence to drug therapy; 3) to compare the number of days on sickness leave due to any cause according to adherence to drug therapy; 4) to estimate prevalence of use of the four drug treatments; and 5) to describe the posology prescribed for the four drug treatments.

## Methods

### Study design

The study is a population-based retrospective cohort study.

### Study Period

Inclusion period was between 2006-2015. The follow-up period was up to 2016.

### Study Population

The study population includes individuals ≥18 years with an incident diagnosis of ACS during the study period 2006-2015, with at least two months of follow-up in the Information System for Research in Primary Care (SIDIAP) [12] after the index date. The next patients will be excluded: pregnant women on the index date; patients with a recorded diagnosis of ischaemic stroke in the six months prior to index date; patients living in a nursing home on the index date; and patients with Alzheimer’s disease or other dementias.

Case definition: patient with an incident diagnosis of ACS registered in CMBD-HA (dataset of diagnoses at hospital discharge) [13] of the Catalan Health Institute (ICS) within the period from 2006-2015. Index date definition: date of ACS episode.

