### Sample Size

The sample will be all patients with a first episode of ACS registered in CMBD-HA of ICS hospitals who meet all inclusion criteria and none of the exclusion criteria during the study period. In a previous study on patients with ACS conducted with SIDIAP database (publication pending) during the period 2009-2011, there were 3415 cases of ACS for all hospitals in Catalonia. Data from CMBD-HA of ICS hospitals corresponds approximately to 30% of all hospitals. Taking into account that our study period is 2006-2015 (10 years), we estimate to find approximately 3400 cases of ACS meeting inclusion criteria for our study.

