### Variables

#### Exposure Definition

Patients will be classified as “exposed” to the study drugs (antiplatelet agents, beta-blockers, ACEI or ARB, statins) if they are prescribed any of them after the episode of ACS (up to two months after the event). The dose prescribed in ECAP will be considered the daily dose used for the patient, and the number of tablets contained in each package will cover the same number of days (see drugs of study in Table 2).

**Table 1 table1:** International Classification of Diseases, Nineth Revision (ICD-9) codes for endpoints of study and procedures.

ICD-9 code	Description
411*	Unstable angina and other forms of acute coronary heart disease
410*	Acute myocardial infarction
433*, 434*, 435*, 436*, 437*	Ischaemic stroke
00.66, 36.03, 36.09, 39.50	Coronary angioplasty

**Table 2 table2:** Anatomical, therapeutic, chemical classification system (ATC) codes for drugs of interest.

ATC code		Description of therapeutic group

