#### Patient Baseline Characteristics

All sociodemographic characteristics will be measured on the index date: index year, number of visits to PHC, age, sex, MEDEA index (socioeconomic deprivation index) [27], smoking status, alcohol intake, height, weight, Body Mass Index (BMI); the information comes primarily from a codified variable. If the patient has no information, it is calculated from height and weight and physical activity.

**Table 3 table3:** ICD-10 codes for comorbidities of interest or diseases for exclusion

ICD-10 code	Description
I24*, I25*	Coronary heart disease
I63*, I65*, I66*, I67.2, I67.8	Ischaemic stroke
G45	Transient cerebral ischaemic attack
I70*, I73*, I74*	Peripheral vascular disease
E78*	Dyslipidaemia
I10*, I15*	Hypertension
E10*, E11*	Diabetes mellitus
I48	Atrial fibrillation
I50*	Heart failure
C00*-C97*	Malignancies
J40*-J44*	Chronic obstructive pulmonary disease
F30*-F39*	Depression
M05*, M06*, M15*-M19*	Arthritis (osteoarthritis or rheumatoid arthritis)
M80*, M81*	Osteoporosis
N18*	Chronic kidney disease
B20*-B24*	HIV
G30*, G31*	Alzheimer’s disease, other dementias

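### The dementia exclusion carries no date, so a diagnosis made after the index ACS can remove a patient, and its code list is narrower than the stated criterion

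*Protocol article*

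**What the plan says.** The Study Population section of the protocol article lists four exclusions. Three have a time anchor: "pregnant women on the index date", "patients with a recorded diagnosis of ischaemic stroke in the six months prior to index date", and nursing-home residence. The fourth has none, as the closing words of the list show: "patients living in a nursing home on the index date; and patients with Alzheimer’s disease or other dementias".

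The Sample Size section gives the only general statement on when exclusions apply. The sample is to meet "none of the exclusion criteria during the study period", and Study Population gives the study period as 2006-2015.

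Table 3 is headed "ICD-10 codes for comorbidities of interest or diseases for exclusion", so it supplies the codes for the exclusion as well as for covariates. Its row "Alzheimer’s disease, other dementias" holds `G30*` and `G31*` only. The only F-chapter codes in the table are `F30*`-`F39*`, for depression. The section on comorbidities and clinical parameters says that the Table 3 conditions are taken at the point nearest the index date, without limiting them to diagnoses made by that date.

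**The concern.** A cohort should be defined by what is known at time zero, here the date of the index ACS. In a retrospective database study the whole record is available when the cohort is built, so an undated exclusion can be run over all of it. A patient then has to survive, and stay in the record, long enough to receive the diagnosis that removes them. The rule takes out survivors' follow-up time, and it can also take out endpoint events that came before the dementia diagnosis. Cognitive decline may be related both to adherence and to death, so the removals need not be balanced between adherent and nonadherent patients. Adjusted Cox models, which the Discussion offers against confounding, cannot restore patients who are no longer in the data.

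The code list raises a different problem. If it is narrower than the criterion, some patients whom the protocol means to exclude stay in.

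**Working it through.** No calculation decides this point. The protocol states no dementia frequency and no figure that depends on the exclusion. Its one planning figure, about 3400 cases, reproduces as 3415 × 0.30 × (10/3) = 3415. It contains no separate term for exclusions and the point does not rest on it. The check is therefore a comparison of the text.

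**Step 1: time anchor of each exclusion (Study Population)**

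| Exclusion | Anchor |
|---|---|
| Pregnancy | Index date |
| Ischaemic stroke | Six months before the index date |
| Nursing-home residence | Index date |
| Alzheimer's disease or other dementias | None |

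**Step 2: does another section supply the missing date?**

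- Sample Size attaches the exclusions to the study period, 2006-2015. For most patients that period runs on past the index date, so the phrase widens the window.
- The comorbidity section takes the record nearest the index date. If a patient's only dementia record is later than the index date, that record is the nearest one. The rule does not prevent a later diagnosis from counting.

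**Step 3: what the literal reading does**

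- Index ACS in 2007, dementia first recorded in 2014. The patient meets an exclusion within 2006-2015 and is removed, although free of recorded dementia for seven years after entry.
- Index ACS in 2007, endpoint stroke in 2009, dementia first recorded in 2012. Follow-up for the composite ended in 2009, yet the patient and the event are both removed because of something recorded three years later.
- The window differs by calendar time. A patient indexed early in 2006 can be removed by a diagnosis made at any time in almost ten years; a patient indexed in 2015 has less than one year. The selection therefore varies with index year, which is itself a listed covariate.

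**Step 4: code list against criterion**

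The criterion covers Alzheimer's disease and other dementias. Table 3 implements it with `G30*` and `G31*`. The section on data sources says that health conditions in SIDIAP are registered as ICD-10 codes. In that classification the dementia categories, including vascular and unspecified dementia, are `F00`-`F03`. The documents do not reproduce ICD-10, so this step relies on the meaning of the codes that the protocol adopts and should be confirmed against the classification. That Table 3 contains none of these codes is visible on its face.

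**Step 5: how the two defects interact**

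The missing date can remove too many patients; the short list leaves too many in. They need not cancel, because they concern different patients. Widening the list without dating the rule would increase the number of patients removed on later information, so the two changes belong together.

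**The case against.** The strongest reply is that this is a wording gap in a condensed article. The look-back window may be set in the full protocol, no section describes a search of the record through the end of follow-up, and taking conditions nearest the index date points towards baseline. The study-period phrase can also be read as qualifying when the ACS occurred, and not when the exclusions are assessed.

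Much of that is fair. The text allows post-index exclusion; it does not state that it will be done. But the article is not merely silent. It dates three exclusions and leaves out the fourth, and its only general timing statement leans the wrong way. Two programmers could build different cohorts from it.

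Three stronger readings are tempting, and the documents do not support them.

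- *The stroke exclusion is also defective.* A reader might compare "I63*, I65*, I66*, I67.2, I67.8" in Table 3 with the Table 1 endpoint list "433*, 434*, 435*, 436*, 437" and infer that unspecified stroke is wrongly left out of the exclusion. The exclusion is worded and labelled as ischaemic stroke, so omitting an unspecified-stroke code contradicts nothing. The lists also serve different sources: hospital discharge data in ICD-9 and primary care data in ICD-10.
- *Table 3 misses most dementia.* The share missed cannot be shown without code frequencies, and the documents give none.
- *The hazard ratio for adherence is biased towards benefit by a known amount.* Any such figure needs dementia prevalence by adherence group and a hazard ratio for dementia, and neither is in the documents. Nursing-home residents are already excluded, and age and the Charlson index are listed as potential confounders, so an unadjusted figure would not describe the planned analysis. It would also say nothing about the undated rule.

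**Conclusion.** The point holds in two parts. The main one is that dementia is the only undated exclusion of four, and the Sample Size wording, taken literally, lets a diagnosis made after the index ACS remove a patient. That would condition cohort entry on post-baseline information. The secondary one is that Table 3 implements the dementia criterion with `G30*` and `G31*` only, which is narrower than its wording. The second part assumes that ICD-10 places dementia categories in `F00`-`F03`.

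Neither the size nor the net direction can be determined from the documents. Removing long survivors, removing earlier events and retaining patients with dementia can move the adherence hazard ratio in different ways, and no frequencies are given with which to weigh them. The case for change rests on an entry rule that permits two different cohorts and on the very low cost of settling it.

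**What to change.** - In Study Population, word the exclusion as dementia recorded on or before the index date.
- In Sample Size, state that exclusions are assessed at or before the index date, in place of the study-period wording.
- State that patients whose dementia is first recorded after the index date stay in the cohort.
- In Table 3, check the dementia row against ICD-10 and complete it by adding `F00*`-`F03*` to `G30*` and `G31*`.

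The cost is one date condition and a code-list edit, made before extraction. The wider codes make the cohort slightly smaller, partly offset by keeping patients diagnosed later. No change to the stroke codes is needed for this point.

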### Data Collection and Data Sources

Diagnoses for study inclusion and endpoints will be obtained from CMBD-HA, which contains diagnoses at hospital discharge from all ICS hospitals, coded with International Classification of Diseases, Nineth Revision (ICD-9) [14]; see Table 1.

The rest of the variables will be captured from SIDIAP, which contains anonymized clinical information of all 279 PHC centres managed by the ICS in Catalonia (North-East Spain), covering a population of more than 5.8 million patients (about 80% of the total of 7.5 million population in Catalonia). The information contained in SIDIAP is registered by PHC general practitioners (GP), nurses and administrative staff in ECAP (electronic health records in ICS): comprehensive sociodemographic information, health conditions registered as ICD10 codes [15], specialist referrals, clinical parameters, toxic habits, PHC laboratory test results, GPs prescriptions and their corresponding pharmacy invoice data registered as Anatomical, therapeutic, chemical classification system (ATC) codes [16], date of sickness leave due to any cause, and date of death. Several reports have shown that SIDIAP data is useful for epidemiological research [17-25]. SIDIAP is listed under the European Network of Centres for Pharmacoepidemiology and Pharmacovigilance (ENCePP) resources database [26].

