### Study Endpoints

ICD-9 codes for primary and secondary endpoints can be seen in Table 1. They will be captured from CMBD-HA database.

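### First ACS and non-fatal endpoints are ascertained only in ICS hospitals, so some prior ACS can enter as incident and recurrences elsewhere count as event-free

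*Protocol article*

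**What the plan says.** Data Collection and Data Sources assigns one source to both entry and outcome: "Diagnoses for study inclusion and endpoints will be obtained from CMBD-HA, which contains diagnoses at hospital discharge from all ICS hospitals". SIDIAP supplies the remaining variables, including the date of death and primary care diagnoses, and is described as "covering a population of more than 5.8 million patients (about 80% of the total of 7.5 million population in Catalonia"). Study Endpoints repeats the rule for the coded endpoints: "They will be captured from CMBD-HA database".

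Study Population defines a case as a "patient with an incident diagnosis of ACS registered in CMBD-HA", and Sample Size says: "The sample will be all patients with a first episode of ACS registered in CMBD-HA of ICS hospitals". Sample Size also gives the reach of the source: "Data from CMBD-HA of ICS hospitals corresponds approximately to 30% of all hospitals".

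The exclusions in Study Population are pregnancy, ischaemic stroke in the preceding six months, nursing home residence and dementia. In Table 3, the only coronary row is coronary heart disease, coded I24* and I25*. No row is labelled AMI or unstable angina, and Study Population does not use the coronary row to exclude anyone.

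**The concern.** Two different things depend on a source that sees only part of the hospital network.

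The first is entry. The cohort is described as first episodes. A patient whose earlier ACS was treated in a non-ICS hospital has no trace of it in the source named for inclusion diagnoses, and no other rule in the article removes that patient. Such patients may already have settled refill habits, which matters when the exposure is adherence over the first eight months.

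The second is outcome. Under Primary Endpoint, a patient with no recorded event is censored at the last date of follow-up. A recurrence admitted outside the ICS hospitals therefore adds event-free time. Death is dated in SIDIAP, so it does not depend on which hospital was used. The components of the composite are then captured unequally, and the one captured best, all-cause death, is the least specific to the four drug groups. The secondary endpoints of AMI, unstable angina and ischaemic stroke are affected directly.

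**Working it through.** **1. The plan's own figure.** Inputs from Sample Size: 3415 ACS cases in all hospitals in Catalonia over 2009-2011 (3 years), an ICS share of about 30%, and a 10-year inclusion period.

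3415 / 3 × 10 × 0.30 = 3415, against about 3400 stated. The figure reproduces. Without the share, 3415 / 3 × 10 = 11,383, so the projection places about 11,383 − 3,415 = 7,968 cases outside the chosen source. Most of these are index events of other people. They show how much hospital activity the source does not see, not how many recurrences this cohort loses.

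**2. Can the loss be derived?** It would need the probability that a patient with an index admission in an ICS hospital has a recurrence admitted elsewhere. The documents do not give it, so what follows is illustration.

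**3. Events missed.** Assumptions: 3400 patients; true composite risk R between 18.9% and 26.3% (the range in the post-AMI cohort cited in the Introduction); a fraction f = 0.5 to 0.7 of first events non-fatal; capture c of non-fatal events; deaths fully captured.

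Missed events = 3400 × R × f × (1 − c). True events = 3400 × 0.189 = 643 to 3400 × 0.263 = 894.

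| Capture c | Share missed, f(1 − c) | Events missed |
|---|---|---|
| 0.9 | 5-7% | 32-63 |
| 0.6 | 20-28% | 129-250 |

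With f = 0.6, the same two capture levels give 0.60 × 0.10 = 6% and 0.60 × 0.40 = 24%. These are upper values for the composite in one respect: a patient with a missed recurrence who later dies still counts, but as a later death.

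**4. Shift towards death.** With f = 0.6, deaths are truly 40% of first events. Among captured events the share is 0.40 / (0.40 + 0.60c): 0.40 / 0.94 = 43% at c = 0.9, and 0.40 / 0.76 = 53% at c = 0.6.

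**5. Effect on the hazard ratio.** By rare-event scaling, the observed non-fatal HR is about the true HR × (capture in adherent / capture in nonadherent). The true value 0.81 is borrowed from the same cited cohort for illustration only.

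- Equal capture: 0.81 × 1 = 0.81, unchanged.
- Capture 0.8 in adherent and 0.6 in nonadherent: 0.81 × 0.8 / 0.6 = 1.08. Reversed: 0.81 × 0.6 / 0.8 = 0.61.
- Composite with 40% deaths fully captured: 0.81 × (0.40 + 0.60 × 0.8) / (0.40 + 0.60 × 0.6) = 0.81 × 0.88 / 0.76 = 0.94. Reversed: 0.81 × 0.76 / 0.88 = 0.70.

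Nothing in the documents shows that capture differs by adherence, or in which direction.

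**The case against.** The strongest reply has four parts.

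*Freedom from prior ACS is already an inclusion requirement, and an article may leave its look-back to the full protocol.* This is partly right. The article does ask for an incident, first episode, and silence about the length of a look-back would be no finding. But the article does name the source for inclusion diagnoses, and that source cannot show an ACS treated elsewhere. SIDIAP codes serve some exclusions as well as comorbidities, as the title of Table 3 says, and the I24*/I25* row could flag some prior coronary disease as a covariate. Neither is used to screen out prior AMI or unstable angina.

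*The 30% is not a leakage rate.* This stands. A reader might infer that about 70% of recurrences are lost. The documents do not support that: the figure is a share of hospitals, used to project case numbers, and many patients may return to the hospital of their index admission.

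*The main objective is an association, and equal capture leaves the HR roughly as it is.* This also stands. A reader might infer that the HR is biased. That needs capture to differ by adherence, for which the article gives no evidence. Absolute incidence, event numbers and the mix of components are affected even with equal capture.

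*Primary care codes would bring errors of their own.* This stands and limits the remedy. Late recording of the index ACS could pass for a recurrence, and recording depends on attending primary care, which may itself follow adherence. Hospital discharge diagnoses are a defensible primary source.

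**Conclusion.** The concern holds as a limitation of the stated source. As written, the plan can admit patients with earlier ACS as incident cases, and it counts recurrent ACS or stroke in non-ICS hospitals as event-free time. Absolute incidence and the non-fatal components are understated, and the composite leans further towards death. The amount is unknown. The 6-24% of composite events is the product of two assumptions (10-40% of non-fatal events admitted elsewhere, 60% of first events non-fatal) and should be read only as a scale. No size can be given for the prior-ACS part. Bias in the adherence HR is possible but not shown. The Discussion names missing data and confounding as limitations, not incomplete event capture. The conclusion assumes that death is taken from SIDIAP, which holds its date; Table 1 has no code for it.

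**What to change.** (a) Make the first-episode requirement operational: exclude patients with any AMI or unstable angina recorded before the index date in SIDIAP or in CMBD-HA, and add the ICD-10 codes for AMI and unstable angina to Table 3.

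(b) Keep CMBD-HA as the primary endpoint source. Add a sensitivity analysis that also counts new, dated SIDIAP diagnoses of AMI, unstable angina or ischaemic stroke. Fix in advance a blanking window after the index date, so that late recording of the index ACS is not counted as a recurrence. Show the CMBD-HA-only result under the same window, so that any difference reflects the source.

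(c) Describe incidence as that of events recorded in ICS hospitals, and add incomplete capture of non-fatal events to the limitations in the Discussion.

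The cost is small: slightly fewer patients, and extra code lists applied to data the study already uses. Primary care dates are less precise, but that weakness is confined to the prior-ACS screen and the sensitivity analysis. Because recording in primary care may itself vary with adherence, the sensitivity result is a second view and not a correction.
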